## Methods

### Study design

COBRA2 is a multicentre, case–control development and validation study. The study involves collection of breath at a single time point from eligible participants and is open to all NHS trusts. The COBRA2 study is sponsored by Imperial College London and has obtained NIHR Clinical Research Network portfolio adoption to support study recruitment. The COBRA2 study commenced in September 2022 and is due to complete by December 2026.

The following groups of participants are being recruited:i)Control group: symptomatic patients who are attending a planned colonoscopy referred under the suspected lower GI cancer pathway. Any patient who is found to have histologically-proven CRC on colonoscopy will be analysed as part of the CRC group.ii)CRC group: patients who either have a confirmed diagnosis of colorectal adenocarcinoma according to a biopsy, or who are due to undergo surgical resection for suspected CRC (with histological confirmation to follow within three months).

The target recruitment for the development of the CPM is 720 patients (470 controls, 250 CRC), aiming for a total of 576 patients (376 controls, 200 CRC) with reliable and complete data (breath test and reference test). For the narrow validation, the target recruitment is up to 250 patients (125 controls, 125 CRC), aiming for 200 patients (100 controls, 100 CRC) with reliable and complete data.

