### Sample size

We have powered our study on sensitivity given the poor prognosis of CRC and the clinical importance of minimising missed diagnoses. The sample size calculation aimed to estimate sensitivity and specificity to acceptable precision using a one-sided Binomial test against a fixed target sensitivity. This was implemented using the R package pwr [26]. Sample size was explored for target sensitivities of 85% to 95% and specificities of 80% to 90%, based on the results from the COBRA1 study. For a target sensitivity of 90%, a sample of 200 CRC cases yields 90% power for the lower (one-sided) 95% confidence interval (CI) limit to be ≥ 83%. For a target specificity of 85%, based on the published specificity for FIT at 10 µg/g, a sample size of 262 controls provides 90% power for the lower limit of the 95% CI to be ≥ 78%. Additional controls (total 376) are included to allow assessment of heterogeneity. Reliable and complete data is therefore required in 576 patients (376 controls, 200 CRC). To account for 20% attrition (e.g., incomplete colonoscopy or breath data), we will recruit a total of 720 patients (470 controls and 250 CRC cases) for CPM development. This sample size allows us to estimate the AUROC with a standard error of less than 2% provided it is at least 0.8, and provides acceptable power for estimating other performance measures. Sample size estimation is consistent with methods suggested by Riley et al. [27] for development of diagnostic models. In the narrow validation study, we aim to recruit an equal number of CRC cases and controls, and similarly allow for a 20% attrition rate. The calculated sample size of up to 250 patients (125 controls, 125 CRC), based on the target sensitivity and specificity (85% to 90%), will ensure sufficient precision in estimating diagnostic accuracy (standard errors for sensitivity and specificity 3.5% to 5%), discrimination (standard error for AUROC < 3%), and calibration (standard error for observed/expected cases < 7.5%), whilst maintaining feasibility [28].

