### Breath sample collection

Participants will be asked to provide a breath sample (up to 2 L) by exhaling directly into a single-use breath collection bag via a mouthpiece that is subsequently sealed. A breath sampling system will pump breath from the bag onto two TD tubes, with a double-bed sorbent phase composed of Tenax TA/Carbograph 5TD (Markes International Ltd, Llantrisant, UK), within an air-tight system at a controlled flow rate of 200 ml/min [29]. This process will be repeated, and the room air will then be sampled using two further TD tubes to control for potential background environmental contamination. The tubes will be immediately sealed with airtight brass caps and transported to the Imperial VOC laboratory for same day mass spectrometry analysis. When analysis is not possible within 48 h, TD tubes will be dry purged prior to storage at −80 °C for subsequent analysis.

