### Statistical analysis

The COBRA2 study is a development and narrow validation study which follows the validation strategy described by Cowley et al. [30] and Transparent Reporting of a multivariable prediction model for Individual Prognosis Or Diagnosis (TRIPOD) guidelines [31]. This method ensures the development of a rigorous and robust CPM that maximises the potential benefit on patient care and decision-making in clinical practice. For development and validation, we use a case–control design for efficiency given that CRC has a low prevalence in the population. Patients referred on the suspected lower GI cancer pathway have a CRC risk of approximately 5–7% [32]. We will use statistical methods for model development and validation. Initially, we will confirm previously identified VOCs using enhanced measurement methods. Using VOCs from COBRA1 as a base, a screening step will identify the most promising additional predictors. Then logistic regression methods will be used to develop a model based on the breath test alone, including all identified VOCs. To reduce over-fitting, we will use model reduction methods such as the elastic net, least absolute shrinkage and selection operator (LASSO) or Harrell’s stepdown approach [33]. For internal model validation, the following will be used [33, 34]:10-fold cross-validation and median values of the performance measures across folds.For calibration, predicted risks of CRC will be plotted against the observed risks.For overall predictive performance Mean Absolute Prediction Error will be estimated (0%: perfect prediction, 100%: no predictive value).For discrimination, the non-parametric AUROC will be calculated, and the threshold that achieves the best trade-off between sensitivity and specificity will be extracted.

For final models, we will use logistic regression modelling to also include patient and clinical characteristics. We will assess linearity of relationships between CRC risk and continuous variables, and explore categorical variables and two-way interactions, including interactions with the breath test. All candidate predictors will initially be entered into the model, before simplification based on Wald statistics (significance < 0.05), size of the predictive weight (odds ratio) and clinical opinion. If there are missing patient or clinical characteristics, we will consider using imputation techniques [35].

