**Fig. 2 Fig2:**
[figure not shown]
Integration of patient and public involvement (PPIE) and equality, diversity and inclusion (EDI) strategy in the COBRA2 study, based on the different stages of the research cycle [37] and the NIHR Research Design Service EDI toolkit [38]. Abbreviations: CRC, colorectal cancer; GRIPP2, guidance for reporting of patient and public involvement; PAG, public advisory group; PIRIT, Public Involvement in Research Impact Toolkit; PIS, participant information sheet; TMG, trial management group

We will also adopt an equality, diversity and inclusion (EDI) strategy throughout the COBRA2 study. We will be recruiting participants from several UK hospitals to ensure we capture a diverse patient population. The team will draw upon the INCLUDE Ethnicity Framework [39] and the Trial Forge Guidance 3 [40] to identify potential challenges and solutions related to ethnic group participation. For example, we will engage in outreach activities with under-served groups in research, through community events and workshops, to build trust in diagnostic testing. Demographic representation analysis will also be performed to assess participant diversity across age, gender, ethnicity and geographical locations. We will ensure our study materials are clear, accessible, and offered in various formats including paper and digital. If participants are unable to speak English, available NHS translation resources will be used. The PAG will review recruitment numbers to ensure data balance and to address any encountered EDI issues. The PAG will also co-design inclusive and accessible project-related communications and dissemination material (e.g. leaflets, videos, social media).

We will formally assess the impact of PPIE involvement through the Guidance for Reporting Involvement of Patients and the Public (GRIPP2) checklist [41] and the Public Involvement in Research Impact Toolkit [42], (co-designed by our patient and public representative, JH), to reflect on how well we are meeting our aims and identify areas we can improve on. We will also use resources, such as the NIHR Research Design Service EDI toolkit [38] and the Health Inequalities Assessment Toolkit [43], to ensure we carry out EDI in a meaningful, equitable, and sustainable manner throughout the study.

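### Internal validation names no hospital-level step; holding out whole hospitals would cheaply guard against counting site VOC background as CRC signal

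*Protocol article*

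**What the plan says.** The Study design section states: "COBRA2 is a multicentre, case–control development and validation study". It opens the study to all NHS trusts and fixes only overall totals: 376 controls and 200 CRC cases with complete data. The Patient and public involvement section adds: "We will be recruiting participants from several UK hospitals to ensure we capture a diverse patient population".

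Under Participant enrolment, controls are found through trust booking systems and cases through multidisciplinary team meetings. No ratio of cases to controls within a hospital is given.

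The Breath sample collection section treats the sampling environment as a possible source of VOCs and plans a countermeasure: "room air will then be sampled using two further TD tubes to control for potential background environmental contamination". The sections on VOC analysis and Statistical analysis do not say how the room-air values enter the model.

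Internal validation is "10-fold cross-validation and median values of the performance measures across folds". The article does not say whether folds are formed at random, stratified or by hospital, and it names no hospital term. Random forest and deep neural networks are to be explored as well.

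The sample size was derived "using a one-sided Binomial test against a fixed target sensitivity".

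**The concern.** Cross-validation protects against over-fitting only to features that the held-out patients do not share with the training patients. If every hospital contributes to both, a VOC background particular to one hospital is present on both sides of the split. Suppose that hospital also supplies more cases than the others. Its background then predicts CRC in training and again in the held-out fold, and looks like a reproducible cancer signal. Elastic net, LASSO or a more flexible learner does not remove it, because the association is real in these data. It just does not carry over to a new hospital.

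Two things are at stake: the internal estimate of performance, and the choice of VOCs that go forward. The narrow validation uses the same case-control design and the article does not mention new hospitals for it, so it might not expose such markers.

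**Working it through.** **1. The plan's own sizing figures.** The article uses the R package pwr, which works with the arcsine effect size h = 2·asin(√p1) − 2·asin(√p0) and n = ((z0.95 + z0.90)/h)², one-sided.

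- Sensitivity, 90% against 83%: h = 0.2065, n = (2.926/0.2065)² = 200.9. Power at 200 cases is 89.9%.
- Specificity, 85% against 78%: h = 0.1810, n = 261.4, so 262. Power at 262 is 90.1%.

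Both figures reproduce, without any allowance for correlation within hospital. That is a usual planning assumption and is not itself a fault.

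**2. How much could hospital alone predict?** The overall case share is 200/576 = 34.7%, say 0.35. Assume K hospitals of equal size with case shares p evenly spaced around 0.35. A model that recognised the hospital perfectly and knew nothing else would have

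AUROC = 0.5 + 0.5 × Σ(pi − pj) / (K² × 0.35 × 0.65), summed over pairs with pi > pj.

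| Case shares | K = 5 | K = 10 |
|---|---|---|
| all equal | 0.50 | 0.50 |
| 20% to 50% | 0.5 + 0.5 × 1.5/5.69 = 0.63 | 0.5 + 0.5 × 5.5/22.75 = 0.62 |
| 5% to 65% | 0.5 + 0.5 × 3.0/5.69 = 0.76 | 0.5 + 0.5 × 11.0/22.75 = 0.74 |

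These are ceilings for the false signal. They show that it depends on unequal case shares and vanishes without them.

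**3. How much of that does ordinary cross-validation pick up?** The number of hospitals, the VOC intraclass correlation (ICC) and the case shares are not in the article and are assumed. Neither simulation below models room-air correction.

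*First simulation:* 576 patients, 50 VOCs with no relation to CRC, ridge logistic regression, VOC ICC 0.05 to 0.20, 40 runs per setting. AUROC:

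| Setting | Ordinary 10-fold | Hospitals held out |
|---|---|---|
| Equal case shares | no inflation | about 0.50 |
| Shares 20% to 50% | 0.51 to 0.56 | about 0.50 |
| Shares 5% to 65%, 10 hospitals | 0.56 to 0.64 | 0.49 to 0.51 |
| Shares 5% to 65%, 5 hospitals | 0.60 to 0.69 | 0.49 to 0.51 |

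In new hospitals the same models gave 0.50 to 0.52.

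*Second simulation, separately built:* 14 VOCs without signal, 5 or 10 hospitals, 60 runs per setting. With equal case shares, ordinary folds gave 0.48 to 0.51. With unequal shares they gave about 0.52 to 0.60 at VOC ICC 0.05, and up to 0.68 at ICC 0.30 with strong imbalance. Leaving hospitals out kept the value near 0.50 throughout.

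**4. With a real signal.** In the first simulation, 14 of the VOCs were shifted by 0.3 SD, with 10 hospitals and shares of 5% to 65%. New hospitals gave about 0.74, ordinary folds 0.77 to 0.80 and hospital-held-out folds 0.75 to 0.76. Ordinary folds were thus about 0.03 to 0.06 too high (0.77 − 0.74 to 0.80 − 0.74), against 0.01 to 0.02 with hospitals held out. No run was made near the AUROC of 0.91 reported for COBRA1, so the size at that level is not known.

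**The case against.** The strongest reply is that the article is silent on how folds are formed. A condensed article may leave this to the full protocol or analysis plan, neither of which is shown. That stands as far as it goes: nobody can say from this text that the folds ignore hospital. But the article does name its method, and 10-fold cross-validation ordinarily means splitting individuals. Validation by hospital would normally be named as such.

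The second reply is that the study has safeguards: room-air tubes, tube background checks, daily instrument control, a single laboratory, verification with authentic standards, and sampling of both groups in outpatient or pre-assessment clinics. These reduce site differences and should be credited. They do not show that none remain. Tube and instrument checks do not act on the air where the patient breathes, and the use of the room-air values in the model is not stated.

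The third is that transportability is openly deferred to a broad validation (COBRA3) with recalibration. That is true, but it comes after the VOC panel has been chosen and does not correct the internal estimate within COBRA2. The additional controls for heterogeneity alter neither the folds nor the number of cases.

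A reader might also infer that the confidence limit for sensitivity is too narrow, or that the 90% power is wrong. The document does not support this. The Binomial test is a sizing device whose figures reproduce. No section fixes how the final limits are computed or makes 83% a success rule, and no within-hospital correlation of test results is given. At zero correlation nothing changes.

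**Conclusion.** The point holds as a conditional risk with a cheap remedy. Three conditions must meet: VOC background differs between hospitals, room-air control does not remove the difference, and the share of cases differs between hospitals. The article rules out none of them and reports no figure for any.

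If they meet, and folds mix hospitals, the false AUROC in the absence of any signal is about 0.51 to 0.56 at case shares of 20% to 50%. It reaches about 0.69 only under strong imbalance, for which the article gives no evidence. With equal case shares it is nil. All these values rest on an assumed number of hospitals (5 or 10), VOC ICC (0.05 to 0.30) and case shares.

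It would go too far to conclude that the planned model will be biased or that the sample size is inadequate.

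**What to change.** In the Statistical analysis section, beside or in place of the ordinary 10-fold procedure:

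- Add internal-external cross-validation that holds out whole hospitals, merging small hospitals so that each fold contains both cases and controls.
- Repeat VOC screening and model reduction inside each fold.
- Use the same folds for the random forest and deep neural network models.
- Report the case share per hospital, and the AUROC within hospital next to the pooled value.

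In the Sample size section, at most add one sentence saying that the 90% power assumes no within-hospital correlation of test results.

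The cost is analysis wording and computing time. The recruiting hospital is presumably already recorded, and cross-validation by hospital needs no further patients. The downsides are fewer and unequal folds, noisier estimates and possibly less favourable reported accuracy. Holding out hospitals gives no protection against case-control differences that are common to all hospitals.

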Currently, there is limited published data which has assessed the performance of breath VOCs in the detection of CRC [17–23]. In these studies, the performance of VOC-based tests was similar to those of existing stool-based immunohistochemical and DNA tests [24]. However, the potential impact of these studies was limited by sample size, unstandardised methods lacking validation and the non-human origin of some reported VOC markers. In 2022, we completed a discovery study, COlorectal BReath Analysis 1 (COBRA1), which showed the proposed breath test has the potential to detect CRC [25]. A diagnostic model to detect CRC was developed from 855 symptomatic patients (709 controls, 146 CRC) with an area under the receiver operating characteristic (AUROC) curve (± standard error) of 0.91 ± 0.01, sensitivity of 83 ± 2%, specificity of 88 ± 1% and negative predictive value of 96%. This was based on a panel of 14 VOC biomarkers (along with body mass index) identified for CRC. COBRA1 had some limitations that should be acknowledged. This includes heterogeneity of populations and variable use of colonoscopy bowel preparation amongst participants included in the study (although this was not found to be a predictive feature or confounding factor in the VOC-based model). Participants were not sampled if they were receiving any concurrent chemotherapy, but they were not excluded if they had any prior chemotherapy, radiotherapy, or immunotherapy. In addition, the technology was not available at the time to perform robust structural and chemical validation of the VOCs using two-dimensional gas chromatography.

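### The protocol's scale for Mean Absolute Prediction Error is wrong: a calibrated model with no predictive value would score about 45% in the development sample, not 100%

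*Protocol article*

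**What the plan says.** The Statistical analysis section of the protocol article lists what internal validation will use: 10-fold cross-validation with median performance across folds, a plot of predicted against observed risk, the non-parametric AUROC, and one measure of overall predictive performance. For that last item it says: "Mean Absolute Prediction Error will be estimated (0%: perfect prediction, 100%: no predictive value". It states no formula and no scaling to a null model, and it names no other overall measure.

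The breath-only model is fitted to a binary outcome (CRC or control) and yields risks between 0 and 1: "Then logistic regression methods will be used to develop a model based on the breath test alone". The Sample size section fixes the case mix of the analysed development set: "Reliable and complete data is therefore required in 576 patients (376 controls, 200 CRC".

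**The concern.** The two anchors tell the reader how to interpret the number. The lower one is right. The upper one describes a quantity on which a worthless model scores 100%, and mean absolute error between a 0/1 outcome and a predicted risk does not behave like that. If a worthless model scores far below 100%, every reported value looks better than it is.

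A second matter concerns the measure itself. Absolute error on a binary outcome is not a proper score: its expected value is not lowest at the true risk. It can therefore improve when predictions are made more extreme than the data justify. That is an awkward property for the only named overall measure in a plan that also sets out to limit over-fitting by elastic net, LASSO or stepdown.

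**Working it through.** **Inputs.** Development set analysed: 200 cases and 376 controls (Sample size), so φ = 200/576 = 0.3472. Development set recruited: 250 cases and 470 controls, so φ = 250/720 = 0.3472, the same share. CRC risk on the referral pathway: 5–7% (Statistical analysis). AUROC for illustration: 0.91, the COBRA1 value (Background).

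**Step 1: try to reproduce the stated 100%.** Take the measure as named, the mean of |Y − p|, with Y = 1 for a case and 0 for a control, and p the predicted risk.

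- A calibrated model with no information sets p = φ for everyone. Cases (share φ) each contribute 1 − φ and controls (share 1 − φ) each contribute φ. The total is φ(1 − φ) + (1 − φ)φ = 2φ(1 − φ) = 2 × 0.3472 × 0.6528 = **45.3%**.
- More generally, predictions unrelated to outcome with mean m score φ + m(1 − 2φ). Everyone called a control (m = 0): 34.7%. Everyone given 0.5: 34.7% + 0.5 × 30.6% = 50.0%. Everyone called a case (m = 1): 65.3%.
- Predictions from an informative model, randomly permuted across patients, also score 45.3%.

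Uninformative predictions therefore score between about 35% and 65% in this sample. The value 100% arises only if every case is given risk 0 and every control risk 1, which is perfectly reversed prediction. No unscaled version reproduces the stated anchor.

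**Step 2: the null value depends on case mix.** At the pathway risk, 2 × 0.05 × 0.95 = 9.5% and 2 × 0.07 × 0.93 = 13.0%. No fixed percentage can serve as the anchor in every population.

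**Step 3: why the score is improper.** For a patient with true risk r and prediction p, the expected absolute error is r(1 − p) + (1 − r)p = r + p(1 − 2r). This is linear in p, so it is lowest at p = 0 when r < 0.5 and at p = 1 when r > 0.5, not at p = r. This is algebra and needs no model.

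**Step 4: size of the effect.** Assume an equal-variance binormal marker with φ = 200/576. Multiply the full true log-odds (intercept included) by a factor and evaluate by numerical integration:

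| Predictions | AUROC | Mean absolute error | Brier |
|---|---|---|---|
| Calibrated | 0.91 | 22.5% | 0.113 |
| Log-odds doubled | 0.91 | 18.1% | 0.121 |
| Hard 0/1 calls from the calibrated model | – | 15.9% | 0.159 |
| Log-odds halved | 0.91 | 30.4% | 0.126 |
| Calibrated | 0.70 | 40.2% | 0.201 |

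Absolute error falls steadily as predictions become more extreme, while the Brier score worsens. Calling everyone a control (34.7%) also beats a calibrated model with AUROC 0.70 (40.2%).

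**Step 5: the proposed alternative on the same figures.** The null Brier score in development is φ(1 − φ) = 0.227. The scaled Brier score, 1 − Brier/[φ(1 − φ)], is 1 − 0.113/0.227 = about 50% for the calibrated model and 1 − 0.121/0.227 = about 47% with the log-odds doubled. It is 0% for the calibrated null and 100% for perfect prediction.

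**The case against.** **A rescaled measure may be meant.** Mean absolute error divided by that of the null model would have the stated anchors, and the article gives no formula. This lowers certainty about what will be computed. But the text names the unscaled measure and states no scaling, and the rescaled version would still reward extreme predictions.

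**Other planned measures limit the harm.** This stands. A model scoring 45% for want of information would show an AUROC near 0.5 and no relation between predicted and observed risk, and gross over-confidence is what a calibration plot reveals. The measure does not enter the sample size.

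**A reader might infer that the measure will choose between logistic, penalised, random forest and neural network models.** The document does not say so. Simplification of the final models rests on Wald statistics, odds ratios and clinical opinion. The machine-learning methods are explored to see whether they improve predictions, with no criterion named. Misuse in selection is a risk, not a stated rule.

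**A reader might infer that the measure always favours the least calibrated or the over-fitted model.** It does not. In the set-up above, halving the log-odds (badly miscalibrated) raises it to 30.4%, and adding 1 to all log-odds raises it to 25.7%. An over-fitted model also tends to lose discrimination out of fold: AUROC 0.86 with doubled log-odds scores 23.3%, worse than the calibrated 22.5% at 0.91, whereas AUROC 0.88 with doubled log-odds scores 21.3%, which is better. The reward is for extremeness, and whether it wins depends on the case.

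**A reader might extend the error to the 1:1 validation study**, where the null value would be 50%. The text attaches the measure to internal validation only. For the narrow validation, the Sample size section names sensitivity, specificity, AUROC and observed/expected cases.

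**Conclusion.** Wrong as written, of moderate to minor severity. The 100% anchor is false for the measure named. The calibrated no-information value is 45.3% in the development sample, and this follows from the protocol's own case share alone. It would change only if a scaling to the null model were intended, which the text does not state.

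The measure is also improper, and that follows from algebra. The illustrative sizes (22.5% falling to about 18.1%, with Brier rising from 0.113 to 0.121) rest on an assumed binormal marker at AUROC 0.91; the direction does not. The practical consequence is a misread performance figure and a risk of misuse if models are later ranked by it. No stated decision in the plan is shown to be wrong because of it.

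**What to change.** Name the Brier score and the scaled Brier score, 1 − Brier/[φ(1 − φ)], as the overall performance measure in internal validation. State the scale as 0% for no predictive value and 100% for perfect prediction, with the null Brier score of 0.227 in development.

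If Mean Absolute Prediction Error is kept, replace the upper anchor with 2φ(1 − φ), about 45% in the development sample. Report the measure as descriptive and state that it will not be used to choose between models. If a version scaled to the null model was intended, give its formula; the same restriction on use applies.

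The cost is one sentence of analysis text and one line of code. No change to data collection or sample size is needed.
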